# Baden Prevention and Reduction of Incidence of Postoperative Delirium Trial (PRIDe): a phase IV multicenter, randomized, placebo-controlled, double-blind clinical trial of ketamine versus haloperidol for prevention of postoperative delirium

**DOI:** 10.1186/s13063-018-2498-6

**Published:** 2018-02-26

**Keywords:** Postoperative delirium, Delirium prevention, Haloperidol, Ketamine, Randomised clinical trial, NSE, S100β, MMSE, Nu-DESC, ICDSC, DOS

## Abstract

**Background:**

Delirium is a neurobehavioural syndrome that frequently develops in the postoperative setting. The incidence of elderly patients who develop delirium during hospital stay ranges from 10-80%. Delirium was first described more than half a century ago in the cardiac surgery population, where it was already discovered as a state that might be accompanied by serious complications such as prolonged ICU and hospital stay, reduced quality of life and increased mortality. Furthermore, the duration of delirium is associated with worse long-term cognitive function in the general ICU population. This long-term experience with delirium suggests a high socioeconomic burden and has been a focus of many studies. Due to the multifactorial origin of delirium, we have several but no incontestable options for prevention and symptomatic treatment. Overall, delirium represents a high burden not only for patient and family members, but also for the medical care team that aims to prevent postoperative delirium to avoid serious consequences associated with it.

The purpose of this study is to determine whether postoperative delirium can be prevented by the combination of established preventive agents. In addition, measured levels of pre- and postoperative cortisol, neuron specific enolase (NSE) and S-100β will be used to investigate dynamics of these parameters in delirious and non-delirious patients after surgery.

**Methods/design:**

The Baden PRIDe Trial is an investigator-initiated, phase IV, two-centre, randomised, placebo-controlled, double-blind clinical trial for the prevention of delirium with haloperidol, ketamine, and the combination of both vs. placebo in 200 patients scheduled for surgery. We would like to investigate superiority of one of the three treatment arms (i.e., haloperidol, ketamine, combined treatment) to placebo.

**Discussion:**

There is limited but promising evidence that haloperidol and ketamine can be used to prevent delirium. Clinical care for patients might improve as the results of this study may lead to better algorithms for the prevention of delirium.

**Trial registration:**

ClinicalTrials.gov, NCT02433041. Registered on 7 April 2015.

Swiss National Clinical Trial Portal, SNCTP000001628. Registered on 9 December 2015.

**Electronic supplementary material:**

The online version of this article (10.1186/s13063-018-2498-6) contains supplementary material, which is available to authorized users.

## Background

First described more than half a century ago [1], numerous risk factors for delirium have been detected over the last decades [3], emphasising the importance of delirium prevention. Despite of being focus of long lasting research, [4–9] incidence remains high [10, 11]. While study data offer some possibilities, there are no strictly defined rules of action for pharmacological or neuropsychological prevention for delirium in general [12]. Hospitals have various algorithms for prevention and treatment of delirium. This randomised, double-blind, placebo-controlled study aims to compare haloperidol [13] and ketamine [13, 14], two agents that have been suggested to prevent postoperative delirium, separately and in combination.

As with all pharmacological treatment options, drug side effects have always to be taken into consideration and careful observation of patients is mandatory. Common side effects of haloperidol include agitation, sleep disorders, extrapyramidal symptoms, overshooting body and extremity movements and headache. Frequent side effects of ketamine include psychiatric disorders (wake-up reactions such as hallucinations, vivid dreams, nightmares, confusion, motor restlessness, conspicuous behaviour and agitation), neurological disorders (nystagmus, tonic and clonic movements, increased muscle tone and elevated intracranial pressure except for controlled ventilation), eye disorders (diplopia, visual disturbance), cardiac problems (tachycardia, hypertension), respiratory problems (elevated respiratory rate), gastrointestinal symptoms (nausea and vomiting) and cutaneous symptoms (erythema, morbilliform exanthema).

While haloperidol seems to be the drug most often administered for delirium prevention [15] and treatment [12], ketamine demonstrates anti-inflammatory properties that might explain its beneficial effect on limiting delirium emergence [16]. A recently published study found that the administration of a sub-anaesthetic dose of ketamine in patients aged 60 years or older undergoing major surgery did not reduce the incidence of postoperative delirium or affect postoperative pain [17]. In this study, the findings were contrary to the trial hypothesis and conflicted with previously published evidence and guidelines [8, 10, 18].

## Methods

### Study setting

Patients are recruited in the anaesthesiology departments of the Cantonal Hospital of Baden and the University Hospital of Basel in the preoperative setting. We adhered to the standard protocol items: recommendation for interventional trials (SPIRIT) figure in preparing the schedule of enrolment, interventions and assessments (see Fig. 1) and the SPIRIT checklist for recommendations for standard protocol items for interventional trials (see Additional file 1).

**Fig. 1 Fig1:**
[figure not shown]
Study period overview (SPIRIT figure)

### Eligibility criteria

#### Inclusion criteria

Patients undergoing either elective or emergency surgery can be screened for eligibility. Participants fulfilling the following inclusion criteria are eligible for the study:Adult patients age 65 years or olderScheduled for surgery within the following fields:○ Visceral○ Orthopaedic○ Vascular○ Gynaecological○ Cardiac○ ThoracicReceive general or combined anaesthesia for their surgerySigned informed consent agreement

#### Exclusion criteria

Participants meeting the following criteria are excluded from the study:Delirium upon hospital admission or during the course of the hospital stay or Mini Mental State Examination (MMSE) score < 24 points or a Delirium Observation Screening Scale (DOS) score ≥ 3 pointsDementiaHigh risk of postoperative treatment in the intensive care unit (ICU) (standard procedure excluded)Known haloperidol or ketamine intoleranceLack of cooperation or lack of communication possibilities○ Speech disorders○ Isolation○ Aphasia○ Coma○ Terminal illness○ Drug or alcohol abuseQT interval (QTc) prolongation (≥ 460 ms in men, ≥ 470 ms in women) or drugs influencing QT interval (see Appendix)Parkinson’s diseaseParkinsonismIntake of dopaminergic drugs (levodopa, dopamine agonists)EpilepsyDelay of surgery for > 72 h after set indication for surgeryBody weight > 100 kgPatient is unable to read German

### Interventions

Participating patients are randomly allocated to one of four study groups: one receiving haloperidol, one receiving ketamine, one receiving both haloperidol and ketamine, and one receiving placebo (Table 1). Patients are administered the active comparator or the placebo comparator only once right before the induction of anaesthesia. Three follow-up days are scheduled beginning on the first postoperative day.

**Table 1 Tab1:** Overview of treatment arms

Treatment arms	Assigned interventions
Active comparator: haloperidol	Haloperidol 0.005 mg/kg body weight at induction of anaesthesia
Active comparator: ketamine	Ketamine 1 mg/kg body weight at induction of anaesthesia
Active comparators: haloperidol + ketamine in combination	Haloperidol 0.005 mg/kg body weight + ketamine 1 mg/kg body weight at induction of anaesthesia
Placebo comparator	Normal saline (NaCl 0.9%)

The study period consists of enrolment, allocation, post-allocation and closeout (Table 2). Allocation is defined as the time point at which the patient is randomised to one of the four treatment arms. Closeout is defined by either the last day of in-hospital follow up or the follow up assessed by a telephone call in the case of preterm hospital discharge.

**Table 2 Tab2:** Weight-dependent dosing

Haloperidol: 5 μg/kg body weight diluted in NaCl 0.9%, haloperidol 5 mg/ml concentrate					
Weight (kg)	Haloperidol (mg)	NaCl (ml)	Weight (kg)	Haloperidol (mg)	NaCl (ml)
40–50	0.5	19.5	71–80	0.8	19.2
51–60	0.6	19.4	81–90	0.9	19.1
61–70	0.7	19.3	91–100	1.0	19.0
Ketamine: 1 mg/kg body weight diluted in NaCl 0.9%, ketamine 50 mg/ml concentrate					
Weight (kg)	Ketamine (mg)	NaCl (ml)	Weight (kg)	Ketamine (mg)	NaCl (ml)
40–50	50	19.0	71–80	80	18.4
51–60	60	18.8	81–90	90	18.2
61–70	70	18.6	91–100	100	18.0

The investigators will preoperatively and postoperatively test cognitive function with the Mini Mental Status Examination (MMSE), the Delirium Observation Scale (DOS), the Nursing Delirium Screening Scale (Nu-DESC) or the Intensive Care Delirium Screening Checklist (ICDSC) (Fig. 1). In addition, preoperative and postoperative cortisol, neuron specific enolase (NSE) and S-100 calcium-binding protein B (S-100B or S-100β) levels will be measured. If the study participant is discharged from the hospital before the scheduled 3 follow-up days are terminated he or she will be contacted by telephone and the conversation will be documented in a free-text field on the case report form.

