### Blinding

Trial participants and care providers including the anaesthesiologist administering the study drug are blinded. The study drugs are prepared as follows to avoid assumption by any colour difference from the placebo (see Table 2 for weight dependent dosing). This adds to a total of 40 ml solution administered slowly to every patient:Trial arm haloperidol: one 20 ml syringe containing the appropriate concentration of haloperidol, and one syringe containing 20 ml NaCl 0.9%Trial arm ketamine: one 20 ml syringe containing the appropriate concentration ketamine, and one 20 ml syringe containing NaCl 0.9%Trial arm haloperidol + ketamine: one 20 ml syringe containing the appropriate concentration haloperidol, and one 20 ml syringe containing the appropriate concentration ketamineTrial arm placebo: two syringes, each containing 20 ml NaCl 0.9%

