#### Trial medication

Patients enrolled in the trial will be randomised to receive either haloperidol (Haldol®, concentrated 5 mg/ml for intravenous (iv) administration, Janssen-Cilag AG, Zug, Switzerland), ketamine (Ketalar®, concentrated 50 mg/ml for iv administration, Pfizer AG, Zurich, Switzerland), both drugs combined or NaCl 0.9% (NaCl 0.9% B. Braun® for iv administration, B. Braun Medical AG, Sempach, Switzerland) administered right before induction of anaesthesia to prevent postoperative delirium.

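### The haloperidol dose is stated inconsistently: the milligrams in Table 2 are at least twice the stated 5 µg/kg, and the NaCl volumes with a 5 mg/ml concentrate imply about ten times it

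*Protocol article*

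**What the plan says.** The protocol article states the haloperidol dose in several places.

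- Interventions, Table 1: "Haloperidol 0.005 mg/kg body weight at induction of anaesthesia". The same rate is given for the combination arm.
- Interventions, Table 2, header: "5 μg/kg body weight diluted in NaCl 0.9%, haloperidol 5 mg/ml concentrate". This agrees with Table 1, since 0.005 mg is 5 µg.
- Interventions, Table 2, rows: each weight band has a haloperidol amount in mg and a NaCl volume in ml. The line holding the lightest band reads "40–50 0.5 19.5 71–80 0.8 19.2" (two bands side by side), and the line holding the heaviest reads "61–70 0.7 19.3 91–100 1.0 19.0".
- Blinding: the haloperidol arm receives "one 20 ml syringe containing the appropriate concentration of haloperidol" plus a 20 ml saline syringe, for a total of 40 ml in every patient. This section refers to Table 2 for the doses.
- Trial medication: the product is "concentrated 5 mg/ml for intravenous (iv) administration", the same strength as in the Table 2 header.

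The article describes no intermediate dilution of the concentrate.

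**The concern.** A weight-based rate, a milligram amount, a diluent volume, a concentrate strength and a syringe volume are tied together by simple arithmetic. Here they cannot all be true. The article permits three different haloperidol doses, depending on which figure is followed.

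This bears first on safety. Participants are 65 or older, the drug is given intravenously, and the Electrocardiogram section itself cites a correlation between intravenous haloperidol dose and QT prolongation. The statement under Strengths and limitations that no adverse events are expected from the single weight-dependent dose presupposes that the dose is known.

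It bears equally on interpretation. Haloperidol is in two of the four arms. If the dose per kg cannot be established, neither a benefit nor a null result in those arms can be attached to a dose.

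**Working it through.** **Inputs.** Rate 0.005 mg/kg (Table 1 and Table 2 header). Weight bands, mg and NaCl volumes (Table 2). Concentrate 5 mg/ml (Table 2 header and Trial medication). Syringe volume 20 ml (Blinding).

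**Control: the ketamine rows.** Ketamine is 1 mg/kg from a 50 mg/ml concentrate. Drug volume = 20 − NaCl, and dose = drug volume × 50.
- 40–50 kg: (20 − 19.0) × 50 = 50 mg, as printed.
- 91–100 kg: (20 − 18.0) × 50 = 100 mg, as printed.

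All six ketamine rows reproduce exactly, and each equals 1 mg/kg at the top of its band. So the layout means NaCl plus concentrate = 20 ml, with each band dosed at its upper limit.

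**The same method on haloperidol.**
- Rate dose at top of band = 0.005 × upper weight.
- Ratio = printed mg ÷ (0.005 × weight), at the top and bottom of the band.
- Dose implied by the NaCl column = (20 − NaCl) × 5 mg/ml.
- Syringe content if the printed mg is drawn up as concentrate = mg/5 + NaCl.

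| Band (kg) | Rate dose at top (mg) | Printed mg | Ratio, top to bottom | NaCl (ml) | 20 − NaCl (ml) | Implied dose (mg) | mg/5 + NaCl (ml) |
|---|---|---|---|---|---|---|---|
| 40–50 | 0.25 | 0.5 | 2.00–2.50 | 19.5 | 0.5 | 2.5 | 19.60 |
| 51–60 | 0.30 | 0.6 | 2.00–2.35 | 19.4 | 0.6 | 3.0 | 19.52 |
| 61–70 | 0.35 | 0.7 | 2.00–2.30 | 19.3 | 0.7 | 3.5 | 19.44 |
| 71–80 | 0.40 | 0.8 | 2.00–2.25 | 19.2 | 0.8 | 4.0 | 19.36 |
| 81–90 | 0.45 | 0.9 | 2.00–2.22 | 19.1 | 0.9 | 4.5 | 19.28 |
| 91–100 | 0.50 | 1.0 | 2.00–2.20 | 19.0 | 1.0 | 5.0 | 19.20 |

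**First conflict, rate against mg column.** The printed amounts are 10 µg/kg at the top of every band (for example 0.5 mg ÷ 50 kg) and reach 12.5 µg/kg at 40 kg (0.5 ÷ 40). Dosing each band at its upper limit does not explain the factor of 2, because the ratio is already 2.00 at that limit.

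**Second conflict, NaCl column against concentrate.** At 5 mg/ml the printed 0.5 to 1.0 mg occupies only 0.10 to 0.20 ml, so the syringe would hold 19.60 to 19.20 ml rather than 20 ml. If the gap to 20 ml is filled with concentrate instead, the dose is 2.5 to 5.0 mg. That is five times the printed mg and ten times the rate at the top of each band (50 µg/kg), rising to 12.5 times at 40 kg (62.5 µg/kg).

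**What consistent rows would look like at 5 mg/ml.**
- If 5 µg/kg is meant: 0.25 to 0.50 mg, drug volume 0.05 to 0.10 ml, NaCl 19.95 to 19.90 ml.
- If the printed mg is meant: the rate is 10 µg/kg, drug volume 0.10 to 0.20 ml, NaCl 19.90 to 19.80 ml.

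**The case against.** The strongest reply concerns the tenfold figure. In all six rows 20 minus the NaCl volume equals, in ml, the printed mg. That is the pattern a preliminary dilution to 1 mg/ml would produce, and with it the mg column, the NaCl column and the 20 ml syringe would agree. The tenfold dose arises only if a preparer disregards the printed mg and tops up with undiluted concentrate. This stands as far as it goes: the tenfold figure is conditional, and it may never have been given. But the article states no such dilution and twice gives the strength as 5 mg/ml. Even granting the dilution, the printed mg remains twice the stated rate.

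Second, a journal article is not the working preparation sheet. It was published in February 2018, 171 patients had been recruited by August 2017, and preparation was checked by a study team member. Nothing in the document shows that anyone received a wrong dose. That is also right, and it is why the records need checking. It does not excuse the article, because the complaint is about printed figures that contradict each other, not about detail left out.

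Third, the blinding consequence is small. A short syringe would lack 0.4 to 0.8 ml, or 1 to 2% of the 40 ml total, and a short syringe and the tenfold dose cannot occur together. The point does not rest on it.

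**Conclusion.** The concern holds and must be fixed. The haloperidol figures are mutually inconsistent as printed:

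- At 50 kg they give 0.25 mg by the stated rate, 0.5 mg by the mg column and 2.5 mg by the NaCl column.
- At 100 kg they give 0.5, 1.0 and 5.0 mg.
- The ratio is 1 : 2 : 10.

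The factor of 2 follows directly from the printed rate and amounts. The factor of 10 assumes a 20 ml fill with the stated 5 mg/ml concentrate and no intermediate dilution; the ketamine rows support the 20 ml reading.

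The two haloperidol arms are affected, 100 of 200 planned participants. Of the 171 recruited, equal allocation (an assumption) would put about 171 ÷ 2 ≈ 85 in those arms. The document does not show which dose they received.

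**What to change.** 1. Reconcile Table 1, the Table 2 header, the mg column, the NaCl column, the concentrate strength and the 20 ml syringe into one instruction, and issue it before any further preparation. If a dilution to 1 mg/ml is used, state it as a step. Which dose is correct is for the sponsor and the competent bodies to decide.
2. Check the preparation records to establish what participants already recruited to the haloperidol arms received, and notify the competent bodies of the discrepancy and what the check shows.
3. Report the actual dose per kg in both haloperidol arms with the results.

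The cost is a corrected table, a review of existing records and a notification. Design, sample size and analysis are unchanged.

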### Outcomes

#### Primary outcome measure

Superiority of one of the active comparator treatment arms in patients after surgery for prevention of hypoactive, hyperactive or mixed delirium, which is assessed by 2-point drop in MMSE score when assessed during one of the 3 postoperative days.

#### Secondary outcome measures

Incidence of postoperative delirium based on cognitive testing and laboratory parameters:A 1-point drop in Nu-DESC score on 1 of the 3 postoperative daysSignificant elevation of study-specific laboratory values after surgery:○ Elevation of NSE above 16.3 μg/l (normal value)○ Elevation of S-100β above 0.1 μg/l (normal value) or doubling of the preoperative value○ Elevation of cortisol level above 638 nmol/l (upper limit of normal range)

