#### Delirium assessment tools

For delirium assessment, the MMSE, DOS and Nu-DESC will be assessed preoperatively to avoid inclusion of patients suffering from cognitive decline prior to surgery. These three tests will be assessed daily one first 3 postoperative days to document the course after surgery and to detect the potential development of postoperative delirium. The MMSE and Nu-DESC will be assessed once daily, and the DOS will be assessed during every nursing shift. Data collection forms are available online in German and English.

The MMSE score is an assessment tool used in nearly all medical fields. The MMSE is a 30-item checklist of symptoms suggestive of cognitive decline. Patients lose 1 point for each symptom that manifests during the specified time frame: 1 point is taken if the question cannot be answered, if it is answered incorrectly or if the demanded task cannot be executed by the patient. Overall, orientation in time and place, retentiveness, short-term memory, language and text comprehension, presence of agraphia, apraxia, agnosia, and executive functions (e.g., action planning) are evaluated. A total of 30 points can be achieved. No cognitive decline is suspected in patients who achieve 27 points. A total of 26 points is considered the threshold value. A total MMSE score of fewer than 24 points is indicative of cognitive limitations. Therefore, patients with an MMSE score below 24 points or a DOS score of at least 3 points preoperatively are not recruited for the study.

The DOS represents a screening tool that has been specifically developed for the assessment of conspicuous behavioural traits suggestive of cognitive decline by the nursing team responsible for the care of a patient. It is based on observations made according to a 13-item checklist that is used during every shift, usually over a period of 3 days. In our study, the DOS score is assessed preoperatively and on postoperative days 1–3. One condition for DOS score interpretation is the assessment of an additional tool for the estimation of cognitive function when the DOS score suggests cognitive decline (i.e., DOS score ≥ 3 points) [19].

The Nu-DESC is a delirium screening tool that has been translated into German in accordance with the guidelines [20]. Based on the Nu-DESC assessment tool, Gaudreau et al. have developed an easy-to-use, nursing-based measurement tool that can be easily integrated in everyday practice [20].

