#### Laboratory assessments of cognitive function

##### NSE

Elevated NSE can be measured in the blood (half-life of roughly 48 h) or the cerebrospinal fluid (half-life of 6–8 h) and is indicative of various pathological conditions. It serves as a marker of acute neuronal lesions as in anoxia, acute brain injury, or inflammatory processes leading to cell destruction. NSE levels are negligible after damage to extracerebral tissue. NSE is quantified in acute brain injury, subarachnoid haemorrhage, stroke, status epilepticus, dementia, active multiple sclerosis, severe central nervous system (CNS) infection, decompensated hypertension, intracerebral and extracerebral neoplasia, cardiopulmonary bypass during heart surgery, cardiac arrest, and neurological metabolic diseases for course documentation and prognostic evaluation.

Although elevated NSE is associated with above-mentioned conditions, Rasmussen et al. identified a significant decrease in NSE after abdominal surgery in a study of 65 patients, but this did not correlate with cognitive dysfunction [22]. Other studies with larger cohorts also showed no difference in NSE levels in delirious and non-delirious patients after investigation of elderly patients who were acutely admitted after hip fracture [23]. However, other data suggest correlation between elevated NSE and delirium in the ICU population [24]. We conclude that the role of NSE in the diagnosis of delirium and its possibility to evaluate long-term outcome is still unclear and needs further investigation.

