##### Cortisol

Serum cortisol levels have been shown to correlate with both the degree of delirium and the risk of developing it, as stress was found to play a major role in delirium and its pathogenesis postoperatively [39]. Serum cortisol has been suggested to be an important marker of risk of postoperative delirium after cardiac surgery in patients with a preoperative diagnosis of major depressive disorder [40].

Serum cortisol levels depend on the patients’ perioperative stress levels. To date, there remains no clear definition of physiological vs. pathological serum cortisol levels following a certain type of surgery. The present study will analyse cognitive decline or present delirium based on the mentioned scores and correlation between serum cortisol levels preoperatively vs. postoperatively.

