##### Secondary analyses

These consist of the quantification of the incidence of postoperative delirium and measured changes in the assessed laboratory parameters including NSE, S-100β and cortisol, and the lowest Nu-DESC scoring (of at least 1 point) after surgery. The delirium assessment tools will be evaluated for their reliability. It will be compared if the results of the various assessment tools correlate with diagnosis of delirium.

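### The secondary Nu-DESC criterion is worded as a fall, like the MMSE, and raised biomarkers sit inside the delirium definition; the endpoint is probably near-uninformative and the marker comparison circular

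*Protocol article*

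**What the plan says.** Under *Secondary outcome measures* the Nu-DESC criterion is a "1-point drop in Nu-DESC score on 1 of the 3 postoperative" days. *Secondary analyses* refers instead to "the lowest Nu-DESC scoring (of at least 1 point) after surgery".

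On scoring, *Delirium assessment tools* says only this: "The Nu-DESC is a delirium screening tool that has been translated into German". It gives no direction, range or cut-off. For the MMSE the same section does give a direction: "Patients lose 1 point for each symptom that manifests during the specified time frame".

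The Nu-DESC item stands under the lead-in "Incidence of postoperative delirium based on cognitive testing and laboratory parameters". Three laboratory criteria follow under that lead-in: "Elevation of NSE above 16.3 μg/l (normal value"), S-100β above 0.1 μg/l or doubled from its preoperative value, and cortisol above 638 nmol/l. No and/or rule joins the items.

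**The concern.** Two definitions are at issue, both secondary.

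First, a fall in score is the natural event for the MMSE, and the Nu-DESC wording closely tracks the MMSE wording in *Primary outcome measure*. If Nu-DESC instead rises with symptoms, an analyst who follows the text would look for delirium in the one direction in which patients without delirium at entry can hardly move. The two Nu-DESC passages also differ from each other. One is a change from baseline; the other is a postoperative score with a qualifier of at least 1 point, which could mean an absolute value or a change.

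Second, if a raised marker helps to make a patient delirious, a later comparison of marker levels in delirious and non-delirious patients partly compares the markers with themselves.

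**Working it through.** **Plan's own figure.** No figure is attached to the Nu-DESC outcome. The only fully specified calculation is the power of the primary four-group chi-square test (*Primary analysis*). With N = 200, V = 0.0125 and a mean proportion of 0.35, λ = 200 × 0.0125 / (0.35 × 0.65) = 2.5 / 0.2275 = 10.99. On 3 degrees of freedom at the 0.05 level this gives 80.3%, which reproduces the stated 80%. Nothing below enters that calculation.

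**Direction of the instruments** (*Primary outcome measure*, *Secondary outcome measures*, *Delirium assessment tools*):

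| Instrument | Scoring given in the article | Worse is | Event as worded |
|---|---|---|---|
| MMSE | points lost per symptom; below 24 is abnormal | lower | 2-point fall |
| DOS | 3 or more suggests decline | higher | none set |
| ICDSC | 4 or more is positive | higher | none set |
| Nu-DESC | none | not stated | 1-point fall; lowest score |

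Both delirium screens with a stated direction count upward. Only the MMSE, a general cognitive test, counts downward. So the article's own evidence points to higher being worse for Nu-DESC and to wording carried over from the MMSE. It does not prove it.

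**What a fall rule would detect, if higher is worse.** *Exclusion criteria* removes patients with delirium, MMSE below 24 or DOS of 3 or more, so low baseline Nu-DESC scores are expected. The following assumptions are not in the documents:

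- A share q of patients scores 1 at baseline and the rest score 0. The same share applies independently to each postoperative day.
- A delirious patient scores 2 to 6 on one of the three days.

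The share flagged under each rule (a change of at least 1 point on any of the 3 days) is then:

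- Fall, delirious: baseline 1 and at least one of the two other days at 0, so q(1 − q²).
- Fall, non-delirious: q(1 − q³).
- Rise, delirious: 1, because the peak always exceeds baseline.
- Rise, non-delirious: (1 − q)[1 − (1 − q)³].

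| q | Fall, delirious | Fall, non-delirious | Rise, delirious | Rise, non-delirious |
|---|---|---|---|---|
| 0 | 0% | 0% | 100% | 0% |
| 0.10 | 0.10 × 0.99 = 10% | 0.10 × 0.999 = 10% | 100% | 0.90 × 0.271 = 24% |
| 0.30 | 0.30 × 0.91 = 27% | 0.30 × 0.973 = 29% | 100% | 0.70 × 0.657 = 46% |

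A simulation of 400,000 patients per scenario gave the same percentages. The fall rule flags delirious and non-delirious patients at nearly equal rates, so it says almost nothing about delirium. The last column shows that turning the sign round is not enough: a bare 1-point rise can flag many non-delirious patients, so the positive cut-off has to be chosen and stated.

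**Biomarkers.** The lead-in in *Secondary outcome measures* bases delirium incidence partly on laboratory values. Against it stand:

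- the *Abstract*, where the markers are to be studied in delirious and non-delirious patients, so delirium status must be set independently of them;
- *NSE*: "the role of NSE in the diagnosis of delirium and its possibility to evaluate long-term outcome is still unclear";
- *S-100β*, which calls the evidence inconclusive for delirium;
- *Cortisol*: "there remains no clear definition of physiological vs. pathological serum cortisol levels following a certain type of surgery". That section also judges delirium from the scores and relates cortisol to it;
- *Secondary analyses*, which lists laboratory changes beside delirium incidence and not as part of it.

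**The case against.** The strongest reply is that the article never says Nu-DESC rises with symptoms. That stands: the direction is inferred from DOS, ICDSC and the MMSE-like wording. But the article does more than leave a detail to a fuller document. It states a direction for the event, twice, and that direction goes against the pattern of its other delirium screens.

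A reader might infer that the rule swaps the classes, so that delirious patients become non-events and the reverse, and that an effective drug would look harmful. The documents do not support this. With baselines near the floor the rule mainly flags nobody, or flags both groups at similar rates. If delirium raised the score on all three days, no delirious patient could fall, and a weak inverse association could arise from non-delirious patients who start above zero. The documents give neither the baseline Nu-DESC distribution nor the duration of delirium from which to claim that.

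A reader might also infer that a patient scoring 0, 3 and 1 on the three days would be scored 0 and so missed. That ignores the qualifier of at least 1 point: the lowest score that meets it is 1. The passage is ambiguous, not demonstrably wrong in that case.

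On the biomarkers, it is fair to say that the *Abstract*, *Cortisol* and *Secondary analyses* already treat them as separate from delirium, and that no rule makes a raised marker sufficient on its own. The conflict therefore lies in one lead-in. It still governs the formal outcome definition and should be reconciled. Nothing in the documents makes the listed thresholds wrong as outcomes in their own right.

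**Conclusion.** The point holds in a limited form. The Nu-DESC outcome is worded in the MMSE's direction, its two passages do not match, and neither direction nor cut-off is stated. If higher is worse, as the article's other delirium screens indicate, the written rule would miss most delirium and the secondary endpoint would be nearly uninformative. In the illustration the flagged rates in delirious and non-delirious patients differ by at most 2 percentage points. That size rests on the assumed baseline share of 0 to 30% and a one-day rise in score; the conclusion that a fall rule misses most delirium needs only low baselines and a scale on which higher is worse.

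The biomarker part rests on the text alone. The outcome lead-in conflicts with five other places in the article and, taken literally, makes the marker comparison circular.

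The primary MMSE endpoint and the sample size are untouched.

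**What to change.** Before any analysis:

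1. In *Delirium assessment tools*, state the Nu-DESC scoring direction and the positive cut-off.
2. With the direction confirmed as higher is worse, define the event in *Secondary outcome measures* as an increase from the preoperative score, matched to that cut-off, on any of the 3 postoperative days.
3. In *Secondary analyses*, use the highest postoperative Nu-DESC score, and say whether the 1-point qualifier is a score or a change, so that the two sections describe one endpoint.
4. Move NSE, S-100β and cortisol out from under delirium incidence and list them as separate secondary outcomes. The model used for them can be left to the analysis plan.

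The cost is wording only. Nu-DESC and the markers are already measured before and after surgery. *Trial status* reports 171 patients recruited by August 2017, and analysis is to start only after recruitment ends, so the change should be dated and documented before then; otherwise it would look like a post hoc reversal of an outcome definition.
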